### 2.12 Data collection and management

A data collection group will be established before the initiation of the trial. At least three persons (two data entry clerks and one data administrator) will be employed during the data collection and management. The authorized personnel will enter data using an electronic case report form (CRF) in an EDC-based database (empoweredc, https://www.yunedc.com/). The accuracy of the data entered will be monitored through the quality control tool of the database, and any doubtful data will be rechecked by a third person. The recorded information will be preserved under the database and will be only accessible to the data administrator and other researchers authorized by the principal investigator. Data will not be exported and analyzed until the end of the trial.

### 2.13 Data analysis

All statistical analyses will be performed using the R software (version 4.0.2). The intention-to-treat and per-protocol approaches will be used for the analysis of the primary outcomes. The as-treated analysis will be used for safety analysis. Continuous data will be presented as mean with standard deviation or median with interquartile range. Categorical data will be presented as numbers with percentages. Student’s t-test or Mann-Whitney *U*-test will be used for the comparison of continuous data, while chi-squared test or Fisher’s test will be used for categorical data. For patients in the test group, the paired *t*-test or Wilcoxon signed-rank test will be used to analyze the difference in PBMC data before and after PDT treatment. The analysis of the gene expression profile will follow the standard procedure for transcriptomic analysis, and a protocol will be developed once the specimens are collected. The survival plot will be drawn for PFS using the Kaplan-Meier method. Log-rank test will be used to compare the difference between the two groups, and Cox regression analysis will be performed to estimate the hazard ratio with 95% CI. All statistical tests will be two-sided, and a significant level will be set at 5%.

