### 2.11 Sample size estimation

We calculate the sample size based on the ORR. According to the published report, 48.6% of patients receiving ICI plus chemotherapy had an objective response (Shitara et al., 2020). Thus, we expected the ORR to be 50% in our control group. For the patients receiving PDT in combination with ICI plus chemotherapy, we assume that 85% of patients will obtain an objective response based on the experience from our center. Based on these expected proportions, we use a two-sided type I error of 5% with a power of 80% to determine the required lowest sample size. It is supposed that approximately 20% of patients may drop out of the trial. Considering all of these, a total of 60 patients (30 per group) are planned to enroll.

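### The ORR comparison may use any of three versions of two tests: two miss the stated 80% power even at 30 per arm, and the third can exceed 5% type I error; one pre-named unconditional exact test would avoid both

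*Protocol article*

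**What the plan says.** Section 2.11 of the protocol article makes ORR the sizing outcome: "We calculate the sample size based on the ORR". The control rate is set by "we expected the ORR to be 50% in our control group" and the test-group rate by "we assume that 85% of patients will obtain an objective response based on the experience from our center". The error rates are given as "we use a two-sided type I error of 5% with a power of 80" percent. The dropout allowance is "It is supposed that approximately 20% of patients may drop out of the trial", and the result is "a total of 60 patients (30 per group) are planned to enroll".

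Section 2.7 lists ORR as a primary outcome alongside PFS, whereas the abstract lists it as secondary. Under either reading it is the outcome that fixes the number of patients.

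Section 2.13 gives ORR no test of its own. It falls under a sentence for all categorical variables: "chi-squared test or Fisher’s test will be used for categorical data". No rule says which test applies when, and continuity correction is not mentioned. The same section sets all tests at two-sided 5%, names R 4.0.2 as the software, and plans both intention-to-treat and per-protocol analyses of the primary outcomes.

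**The concern.** With 24 to 30 patients per arm, the tests that section 2.13 allows are not interchangeable. Fisher's test is conservative, so much of the nominal 5% goes unused and power is lost. The uncorrected chi-squared test has more power but does not guarantee 5%. R's standard chi-squared function applies a continuity correction to 2×2 tables unless told otherwise, and this makes the chi-squared test about as conservative as Fisher's. The wording therefore covers three procedures.

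The sample size was promised at 80% power and 5% two-sided error. If no permitted version delivers both, sections 2.11 and 2.13 do not fit together. Some trials would also be declared positive or negative according to the version run. For example, 23/30 responders against 15/30 gives p = 0.032 by uncorrected chi-squared, 0.060 by Fisher and 0.061 by corrected chi-squared. The smallest expected count there is 11, so small cells do not settle the choice.

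**Working it through.** **Inputs.** Control ORR 0.50, test ORR 0.85, two-sided 5%, 80% power, 20% dropout and 30 per arm, all from section 2.11. The evaluable number after dropout is 30 × 0.8 = 24 per arm.

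**Step 1: reproduce the plan's figure.** The normal formula with unpooled variance is n = (z₀.₉₇₅ + z₀.₈₀)² × [p₁(1−p₁) + p₂(1−p₂)] / (p₂−p₁)².

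n = (1.960 + 0.842)² × (0.25 + 0.1275) / 0.35² = 24.19 per arm.

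Then 24/0.8 = 30, or 25 × 1.2 = 30; keeping the decimals, 24.19/0.8 = 30.2. So 60 in total is reproduced, to within two patients under any rounding. The pooled-variance formula gives 27 per arm (34 after dropout, 68 in total). The continuity-corrected formula gives 33 per arm (42 after dropout, 84 in total). The plan's figure thus matches a large-sample calculation without correction.

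**Step 2: exact power and size of each permitted test.** All (n+1)² outcome tables were enumerated, with a test rejecting when its p-value is at most 0.05. Power is the sum of Bin(x; n, 0.50) × Bin(y; n, 0.85) over the rejected tables. Size is the same sum with a common rate p in both arms, maximised over a grid of about 2,000 values of p.

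| Test | Power, 30/arm | Max size, 30/arm | Power, 24/arm | Max size, 24/arm |
|---|---|---|---|---|
| Fisher | 77.7% | 2.7% | 66.8% | 2.9% |
| Chi-squared, corrected | 77.7% | 2.7% | 64.0% | 2.9% |
| Chi-squared, uncorrected | 84.7% | 5.5% | 76.7% | 6.0% |
| Boschloo | 82.1% | 4.7% | 74.7% | 4.9% |
| Barnard (pooled z) | 83.2% | 4.7% | 74.3% | 4.4% |

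**Step 3: how often the permitted tests disagree at the design rates.**
- Uncorrected chi-squared against Fisher: chi-squared alone is significant in 7.0% of trials at 30 per arm and 9.9% at 24. The reverse never occurs.
- Corrected chi-squared against Fisher: at 30 per arm they reject exactly the same tables. At 24 per arm Fisher alone is significant in 2.8% of trials.

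**Step 4: gain and loss from an unconditional exact test.**
- Boschloo against Fisher: 82.1 − 77.7 = 4.4 points at 30 per arm; 74.7 − 66.8 = 7.9 at 24.
- Boschloo against corrected chi-squared: 4.4 points at 30 per arm; 74.7 − 64.0 = 10.7 at 24.
- Boschloo against uncorrected chi-squared: 82.1 − 84.7 = −2.6 points at 30 per arm; 76.7 − 74.7 = 2.0 points lost at 24.

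**The case against.** The strongest reply is that the sentence is a conventional one for all categorical data, and that a selection rule, the correction and the interval for ORR are details for an analysis plan that is not shown. This stands for the either/or wording taken alone, and fully for the confidence interval. A reader might note that PFS gets a hazard ratio with an interval ("Cox regression analysis will be performed to estimate the hazard ratio with 95% CI") while ORR does not, and infer a gap. That is a reporting detail and no part of this point.

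A reader might also infer that chi-squared and Fisher always differ by 7 to 10 points of power. They do so only with the correction switched off, which the article does not say.

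The usual convention, Fisher only when an expected count is below 5, is not in the article. If it applied, Fisher would be used in about 0.1% of trials at 30 per arm and 1.9% at 24. With uncorrected chi-squared otherwise, power would be 84.7% and 76.6%. That nearly removes the disagreement, but leaves the correction open and the uncorrected test's size unguarded.

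The size excess is modest. At 30 per arm the 5.5% arises at a common rate near 88%, and between 45% and 70% the size is 4.8% to 5.2%. At 24 per arm, however, the 6.0% maximum falls at a common rate of 50%, the plan's control rate. The 24-per-arm figures describe a set after dropout, not everyone randomised.

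The open-label design adds little: a test can be chosen after the event in a blinded trial too, and section 2.12 defers analysis until the trial ends.

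What the reply does not meet is the mismatch itself. An analysis plan that kept to the permitted tests would still have to choose between missing 80% power and risking more than 5% error.

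**Conclusion.** The point holds in limited form. No version of the tests named in section 2.13 gives both the 80% power of section 2.11 and a guaranteed 5% two-sided error. Fisher and corrected chi-squared fall 2.3 points short of 80% (80 − 77.7) with all 30 per arm analysed. Uncorrected chi-squared passes 80% at 30 per arm but can exceed 5%. At 24 per arm none of the tests computed reaches 80%, the unconditional exact tests included, so changing the test does not restore the planned power after 20% dropout.

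It would go too far to say that the better test costs nothing. It costs no patients, but it gives up 2.0 to 2.6 points against the uncorrected test if Boschloo is used, and 1.5 to 2.4 if Barnard is used. Nor do the documents show that anyone intends to pick the test from the data.

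The figures assume the plan's rates of 50% and 85% in the patients analysed, equal arms, and no stratification. The weight is moderate: a correction worth making before data are seen, not a threat to the trial.

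**What to change.** In section 2.13, name one unconditional exact test for ORR at two-sided 5%, for example: ORR is compared between groups by Boschloo's unconditional exact test at the two-sided 5% level, and no other test decides ORR. Barnard's test is an equal alternative; what matters is that one is named. Keep the chi-squared/Fisher sentence for descriptive tables.

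In section 2.11, restate the power for the named test. For Boschloo this is 82.1% at 30 per arm and 74.7% at 24 per arm, with size at or below 4.9%.

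The cost is two short edits before any outcome data are analysed, standard software and no extra patients. The only statistical price is the loss of 2.0 to 2.6 points of power against the uncorrected chi-squared test.

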### 2.14 Data monitoring

The trial process will be monitored by the institutional data safety monitoring committee at regular intervals (at least annually). All event reports of toxicities, treatment discontinuation, and transformation will be recorded and submitted to the data monitoring committee. The primary investigator will decide to continue or abort the trial based on the safety assessment from the data safety monitoring and ethics committee.

### 2.15 Confidentiality

All participants will be allocated a unique code for identification once they are included. All specimens and forms will be securely maintained, and electronic data will be stored in the database with an encryption technique. Only authorized personnel can access the data. The personal information of participants will be confidential and never shared with any third-party organizations. The primary investigator is the person who is finally responsible for the security of the data.

## 3 Discussion

Although a lot of previous studies have demonstrated an enhanced immune response by PDT, almost all of them are preclinical evidence from animal models (Krosl et al., 1995; Cecic et al., 2006; Wang et al., 2013; Li et al., 2019). Further high-quality evidence from randomized control trials is needed to clarify the immune-stimulated role of PDT in a clinical condition. Here we perform a randomized control trial grouped by PDT in combination with ICI plus chemotherapy versus ICI plus chemotherapy, aiming to evaluate the synergistic effect of PDT with immunochemotherapy. Successful implementation of this trial will help to find an immunologic adjunct for ICIs-based therapy. At present, the scheme of ICI plus chemotherapy is used as a first-line treatment for patients with metastatic gastric cancer, but the efficacy of this combination is still limited, especially in patients with unclear PD-L1 status. In the KEYNOTE-062 study, pembrolizumab plus chemotherapy was shown no superiority to the chemotherapy alone in gastric cancer patients with a PD-L1≥1 (Shitara et al., 2020). Another study (ATTRACTION-4) evaluated the combination of nivolumab plus chemotherapy in an Asian population. PD-L1 expression is not used as the criterion for the selection of patients in this study, and better results were found in the ORR and PFS but not the OS when comparing ICI plus chemotherapy with chemotherapy alone (Boku et al., 2020). Based on these facts, it is meaningful to improve the therapeutic effects of ICI by appending an adjunct. As a well-tolerated treatment in most cancer patients, a combined strategy with PDT will not significantly increase the risks of safety in theory. This is our foundation for conducting this trial.

Our cancer center has rich experience in PDT treatment in digestive tract tumors, which will provide support to assure the subjects receiving a homogeneous treatment in this trial. We used ICI plus chemotherapy as the standard scheme, which is in accord with the beneficence principle in medical ethics. In addition, this gives a promise of enough interested patients for recruitment. In this trial, we will only include patients with age ≤65, and poor health conditions will be excluded. This is based on the consideration that elderly patients with poor conditions are easier to drop out due to their intolerance of the assigned treatments. Decreasing the ratio of drop-outs can avoid the negative influence caused by it on data analysis and increase the validity of our results.

There are also some limitations in this trial. Firstly, chemotherapy will be concurrently applied with ICI in the schemes of this trial. This means this trial can just identify the effects of PDT for ICI combined with chemotherapy. How these effects come and whether PDT can synergize with either of the ICI and chemotherapy or both of them will be hard to explain. In the future, we will conduct further studies to clarify these when the roles of PDT in the tumor microenvironment are more demonstrated. Secondly, this is an open-label study, and blinding will not be used during the study. The risk of bias caused by this will inevitably impact the results to some extent. Finally, the sample size is small. It may be difficult to perform subgroup analysis with these subjects.

This trial is the first study to explore the clinical significance of PDT in improving the outcomes of ICI plus chemotherapy in patients with advanced or metastatic gastric cancer. This paper provided an interpretation of its design and methodology. The results of this trial will help us know the roles of PDT in gastric cancer and may give a novel combined strategy for immunotherapy.

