## Abstract

**Introduction:** The immune checkpoint inhibitor (ICI) has been approved as the first-line therapy for metastatic gastric cancer in China. The treatment response of immune checkpoint inhibitor is highly dependent on the immune condition within the tumor microenvironment. Photodynamic therapy (PDT) has a long history in cancer treatment, and recent studies showed it had an immunomodulatory effect on the tumor. Here we will conduct a trial to assess whether or not a combination with Photodynamic therapy will improve the outcomes of immune checkpoint inhibitor-based treatment in patients with advanced or metastatic gastric cancer.

**Methods:** This study is a single-center, open-label, randomized controlled, phase 2–3 trial. Patients (18–65 years old) with untreated gastric or gastroesophageal junction adenocarcinoma will be eligible for this trial. Sixty participants will be enrolled and randomly divided into the test group (*n* = 30) and control group (*n* = 30) to receive photodynamic therapy in combination with immune checkpoint inhibitor plus chemotherapy and immune checkpoint inhibitor plus chemotherapy, respectively. The primary is progression-free survival (PFS). The secondary outcomes include objective response rates (ORRs) and the occurrence of adverse events. In addition, we will also assess the changes in peripheral blood mononuclear cells (PBMCs) and tumor microenvironment after photodynamic therapy treatment in the test group. Evaluation of the tumor response will be performed every two cycles for a maximum of eight cycles.

**Discussion:** Photodynamic therapy has an immunomodulatory effect on the tumor microenvironment; however, this has not been demonstrated for gastric cancer in a clinical trial. Based on our experience of photodynamic therapy treatment in digestive tract tumors, we plan to conduct a randomized controlled trial on this topic. This will be the first study to evaluate the synergistic effect of photodynamic therapy with immunochemotherapy for patients with advanced gastric cancer.

**Ethics and dissemination:** It was approved by the Institutional Research Ethics Committee of Lanzhou University Second Hospital (No. 2022A-491). When this trial is completed, it will be shared at conferences and submitted for a potential publication in a peer-reviewed journal.

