### 2.7 Outcomes

The primary outcomes are objective response rate (ORR) and progression-free survival (PFS). The best overall response from ICI plus chemotherapy initiation to disease progression or last follow-up will be used to analyze the ORR. ORR refers to the proportion of patients with complete response (CR) and partial response (PR). PFS is defined as the time from ICI plus chemotherapy initiation to the date of first documented tumor progression or death no matter which happens first. All evaluations of treatment response or progression will be conducted by experienced radiologists according to the RECIST 1.1 criteria (Eisenhauer et al., 1990). The safety will be assessed using the incidence of adverse events defined as any toxicity from intervention initiation to the study end according to the NCI-CTCAE 5.0 criteria (Institute, 2017). For patients who receive PDT treatment, a self-control assessment before and after PDT will be performed, in which the changes in peripheral blood mononuclear cells (PBMCs) and intratumoral gene expression profiles will be evaluated.

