### 2.8 Investigation methods

The tumor will be assessed using contrast-enhanced CT of the abdomen at baseline and each following visit for all included patients. According to the NCI-CTCAE 5.0, any adverse event during the study will be recorded with their types, severity, start and end time, and relatedness to interventions. Blood and tumor tissue specimens before and after PDT will be collected from PDT-treated patients for corresponding tests. After the pre-processing of the blood specimens, PBMC analysis will be performed using flow cytometry to detect the following cells: total T lymphocytes (CD3^+^), cytotoxicity T cells (CD8^+^), CD4^+^ T cells (CD4^+^), and T regulatory cells (Tregs, CD4^+^ CD25^+^ FOXP3^+^). Specimens of tumor tissues will be assessed with an RNA-seq test to investigate the spatiotemporal changes in the expression profile. All patients will receive tumor histological examination [HE stain and immunohistochemistry (IHC)], routine laboratory studies, ECG, chest X scan, ECOG scoring, physical examination, and records of vital signs and concomitant medications. The work timeline and corresponding investigated items are listed in Table 1.

**TABLE 1 T1:** Schedule for the important events in this trial.

Items	Screening phase (within 1 week)	Treatment phase				Follow up phase
		Test group			Control group	
		Cycle 1 (before PDT)	Cycle 1 (after PDT and before ICI plus chemotherapy)	Cycle 1 and beyond (day 1 for ICI plus chemotherapy)	Cycle 1 and beyond (day 1 for ICI plus chemotherapy)	
Informed consent	X					
Inclusion and exclusion criteria	X					
Tumor histological examination	X					
Medical history	X					
Physical examination	X			X	X	X
Vital signs	X			X	X	X
Performance status (ECOG)	X			X	X	X
Concomitant medications	X			X	X	X
Electrocardiogram (ECG)	X					
Chest X scan	X					
Laboratory tests (including blood routine examination, chemistry test, coagulation function, tumor marker, and thyroid function)	X			X	X	X
Pregnancy test (women only)	X			X	X	X
Photosensitizer injection and skin test		X				
Collection and analysis of blood and tumor tissue specimens		X	X			
Tumor assessment by CT	X		X	X (in the cycle 2, 4, 6, and 8)	X (in the cycle 2, 4, 6, and 8)	X
Adverse events assessment		Continuously				X

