### 2.10 Allocation and blinding

Patients will be randomly allocated into the test group and control group at a ratio of 1:1. An independent researcher who will not take roles in patient recruitment will generate a random sequence table using the R software, and the paper strips with allocation results will be kept in a non-transparent envelope. Once the patient is recruited, the doctor will assign the interventions according to his allocated group. As it is difficult and almost impossible to set blind for PDT treatment, this trial is set as open-label.

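### The reason given for open-label treatment does not cover the CT readers, whose unmasked RECIST readings decide ORR and the progression part of PFS

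*Protocol article*

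**What the plan says.** On who reads the images, section 2.7 says: "All evaluations of treatment response or progression will be conducted by experienced radiologists according to the RECIST 1.1 criteria". It mentions neither masking of these readers nor independent review. Section 2.8 adds the modality: "The tumor will be assessed using contrast-enhanced CT of the abdomen at baseline and each following visit for all included patients".

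On blinding, section 2.10 gives its reason in one sentence: "As it is difficult and almost impossible to set blind for PDT treatment, this trial is set as open-label". The limitations in the Discussion go further: "Secondly, this is an open-label study, and blinding will not be used during the study". They then concede: "The risk of bias caused by this will inevitably impact the results to some extent". No mitigation follows.

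On the endpoints, section 2.7 names ORR and PFS as primary, while the Abstract names PFS alone and lists ORR as secondary. PFS runs to "first documented tumor progression or death no matter which happens first". The sample size in section 2.11 rests on ORR: 50% in the control arm against 85% with PDT, the latter taken from the centre's own experience.

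On scan timing, Table 1 gives the test group a CT after PDT and before immunochemotherapy that has no counterpart in the control column. Section 2.9 likewise places the first tumour assessment after PDT for patients who receive it.

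**The concern.** Section 2.10 argues from the delivery of PDT. Patients and endoscopists cannot be blinded to a laser procedure, but a radiologist can measure lesions on a coded CT series without knowing the arm. For the image readings, the word inevitable therefore does not follow from the reason given.

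The readings involve judgement. Choosing target lesions, measuring diameters, separating partial response from stable disease and calling new lesions can all drift with expectation. Here expectation points one way: a single centre, experienced in PDT, that assumes 85% response with it. If readers know the arm, borderline calls may favour PDT, and part of an observed ORR or PFS difference could come from reading rather than treatment.

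**Working it through.** **Does the stated reason reach the readers?** Section 2.10 concerns the PDT treatment. Section 2.7 assigns response and progression to radiologists, and section 2.8 has them work from CT. Section 2.15 gives every participant a unique code. Nothing in these sections prevents coded reading. The Discussion sentence nevertheless excludes blinding throughout the study.

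**The plan's own figure.** Inputs from section 2.11: 50% and 85%, two-sided 5%, power 80%, dropout 20%.

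n per arm = (1.960 + 0.842)² × (0.50×0.50 + 0.85×0.15) / 0.35² = 7.849 × 0.3775 / 0.1225 = 24.2, rounded up to 25.

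25 × 1.2 = 30 per arm, or 60 in total, as stated. Masking the readers changes none of these inputs.

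**Illustration of differential reading in ORR.** The misreading rate m is an assumption. The true ORR is set to 50% in both arms, the plan's control value, with 30 patients per arm.

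- Test arm read up: p_T = 0.50 + 0.50m.
- Control arm read down, where assumed: p_C = 0.50 − 0.50m.
- Rejection probability = sum over all (i, j) of Bin(i; 30, p_C) × Bin(j; 30, p_T), counting the tables in which the test rejects.
- Chi-squared (no continuity correction) rejects if (|i − j|/30) / √(p̄(1 − p̄) × 2/30) > 1.96, with p̄ = (i + j)/60. Fisher rejects if the two-sided p ≤ 0.05. Section 2.13 allows either test.

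| Assumed misreading | Read ORR, test / control | Two-sided rejection, chi-squared (Fisher) | Of which false benefit of PDT, chi-squared (Fisher) |
|---|---|---|---|
| None | 50% / 50% | 5.2% (2.7%) | 2.6% (1.4%) |
| 10%, test arm only | 55% / 50% | 6.9% (3.9%) | 6.0% (3.4%) |
| 15%, test arm only | 57.5% / 50% | 9.2% (5.4%) | 8.6% (5.2%) |
| 10%, both arms, opposite directions | 55% / 45% | 12.4% (7.7%) | 12.1% (7.6%) |
| 15%, both arms, opposite directions | 57.5% / 42.5% | 21.9% (14.8%) | 21.8% (14.8%) |

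With 24 per arm (30 × 0.8), the two-sided figures in the same order are 6.0%, 7.4%, 9.3%, 12.2% and 20.1% by chi-squared, and 2.9%, 3.9%, 5.1%, 7.0% and 12.8% by Fisher.

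**In patients.** About 15 of 30 per arm are non-responders, so 10–15% misreading moves 1.5 to 2.25 patients in one arm, or 3 to 4.5 across both. Near a pooled rate of 50%, chi-squared significance needs a difference of 1.96 × √(2 × 0.25/30) = 0.253, that is 7.6, so 8 patients. Such misreading does not produce significance on its own; it supplies part of the distance.

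**PFS.** No corresponding figure is given, because the document states no PFS assumptions from which to derive one.

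**Would blank request forms be enough?** Per Table 1, a test patient has a screening CT and a post-PDT CT before immunochemotherapy. A control patient has only the screening CT. The number or dates of pre-treatment scans could therefore identify every test patient, even with arm and PDT history removed.

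**The case against.** Four points can be made for the plan.

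1. *The limitation is disclosed, and readings already go to radiologists under a standard criterion rather than to treating investigators.* Both are true, and both help. Neither masks the readers, and disclosure does not make an avoidable bias unavoidable. A journal article may also leave reading procedures to the full protocol. Here, though, the article makes a positive statement that no blinding is used. If the full protocol does mask the readers, that sentence is wrong.

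2. *The misreading rates are invented, and the larger figures need opposite errors in both arms.* This stands. With the test arm alone and Fisher's test, 10–15% misreading gives 3.9–5.4%, close to the nominal level. The full range has to be shown.

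3. *Masking is harder than it looks.* This also stands. The extra post-PDT CT can reveal the arm, and visible local changes may do so too. A reader might infer that stripping labels and request forms is enough and costs almost nothing. The scan schedule does not support that, and the document gives no cost.

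4. *Other open-label bias remains.* Treatment and dropout decisions stay unmasked, and section 2.11 expects 20% dropout. Masked reading addresses only the readings.

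Two stronger readings are tempting and unsupported. One is that both primary outcomes are purely radiologist readings: PFS also counts death, and the Abstract makes PFS the only primary outcome. The other is that a positive result could not be told apart from reader expectation: the modelled bias is 5 to 15 percentage points, against the 35 points assumed in the design.

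**Conclusion.** The point holds in a limited form. The plan declares that blinding will not be used, for a reason that does not extend to image reading. That leaves an avoidable source of bias in ORR and in the progression component of PFS. This is so whichever endpoint is finally primary, although section 2.7 and the Abstract must be reconciled.

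The size is uncertain. Under assumed misreading of 10–15%, a true ORR of 50% in both arms and 30 patients per arm, the two-sided false-positive risk lies between 3.9% and 21.9%, depending on the test and on whether one or both arms are affected. Without misreading it is 5.2% by chi-squared and 2.7% by Fisher. Nearly all of the excess falls in favour of PDT. These figures show sensitivity; they do not estimate the bias that will occur. The change should be made, but the trial is not invalid without it.

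**What to change.** - In sections 2.7 and 2.10, state that the same study radiologists read RECIST 1.1 from coded CT series, with arm, PDT history, scan dates and number of pre-treatment scans hidden.
- Present the same number of baseline series per patient in both arms, so that the test arm's extra post-PDT CT does not reveal allocation.
- State which pre-treatment scan is the RECIST reference. Section 2.7 counts response from the start of immunochemotherapy, and the choice between the screening and post-PDT scans decides whether shrinkage caused by PDT itself counts as response.
- Use the masked readings for both ORR and PFS.
- In the Discussion, replace the sentence that excludes blinding with one saying that treatment is open-label and image reading is masked. Limit the conceded bias to what remains: treatment and dropout decisions, and cases unmasked by visible local changes.

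Cost: administrative work to code the series, hide dates and equalise the baseline sets. No extra reader, scan or patient is needed, and the sample size, significance level and planned power are unchanged. Local PDT changes may still unmask some cases.
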